### Sample size calculation

2.7

Using 80% power for detecting treatment differences, a significance level of 0.05, and assuming a standardized effect difference of 0.7% and a 20% dropout rate, we conclude that a total of 80 patients is needed to ensure statistically significant results.

### Statistical analysis

2.8

Efficacy analysis will be conducted for the intention to treat population primarily according to the full analysis set (FAS) principle and secondarily according to the per-protocol (PP) principle. Missing values will be imputed by the last-observation-carried-forward method. Safety analysis will be conducted by FAS and PP in aggregate. The statistical analysis will be performed using SPSS. *P* < .05 is considered statistically significant.

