### Study procedure

2.4

The participants who provide written consent and meet the inclusion and exclusion criteria will be selected based on results from the demographic information survey, medical history (past, present, family), vital signs (blood pressure, pulse rate, body temperature), physical examination, laboratory tests, and CDR, GDS, K-IADL, MoCA-K, SGDS scores at the screening visit. Eligible participants will be informed via telephone call and will be asked to visit the trial center within 1 week (visit 1). If participants are taking drugs that may affect the trial, a washout period of at least 15 days will be required before trial start. At visit 1, investigator will check the result from the screening period and changes since that period, and subjects will be allocated to the experimental or the control group using a stratified block randomization method. After randomization, the participants will be administered 6000 mg of JDH or placebo product daily for 12 weeks. Both groups will be instructed to consume the tablets orally, 3 times a day before meals. Subsequently, subjects will undergo assessments for primary and secondary endpoints (SVLT-E, RCFT, DST, Calculation, K-CWST, DSC, K-TMT-E, COWAT, K-BNT, MMSE-DS, MoCA-K, PIT-C, EQ-5D, KQOL-AD, cost analysis, CTIS, BPPA, BIA, WED, fNIRS). They will visit the trial center for evaluation of any changes or adverse effects every 2 weeks. Tests and assessments will be performed according to the following schedule: Visit 2 (Blind test); Visit 4 (WED, fNIRS, MoCA-K, PIT-C, EQ-5D, KQOL-AD); Visit 7 (all tests); and Visit 8 (SVLT-E, Cost analysis, MoCA-K, PIT-C, EQ-5D, KQOL-AD). Detailed assessment schedules are outlined in Table 1. A follow up study will be conducted 12 weeks after the conclusion of the trial.

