#### Primary outcome

2.9.1

The primary outcome will be measured by SVLT-E. The primary endpoint will be the change in score from baseline to 12 weeks. For efficacy assessment, we will use the covariance analysis model that includes the SVLT-E scores as covariates and the trial centers as fixed effect variables.

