#### Secondary outcomes

2.9.2

The secondary outcomes will be measured by SVLT-E, RCFT, DST, calculation, K-CWST, DSC, K-TMT-E, COWAT, K-BNT, MMSE-DS, MoCA-K, PIT-C, EQ-5D, KQOL-AD, cost analysis, CTIS, BPPA, BIA, WED, and fNIRS. The secondary endpoints will include change in SVLT-E score from baseline to 24 weeks; change in RCFT, DST, K-BNT, calculation, COWAT, K-CWST, DSC, K-TMT-E, MMSE-DS scores from baseline to 12 weeks; change in EQ-5D, PIT-C, MoCA-K score from baseline to 6, 12, and 24 weeks; and change in KQOL-AD score from baseline to 6, 12, and 24 weeks. The cost analysis (performed at 0, 12, and 24 weeks), CTIS, BPPA, and BIA values (0, 12 weeks), and WED and fNIRS values (0, 6, 12 weeks) will also be secondary endpoints. For efficacy assessment of SVLT-E, MMSE-DS, EQ-5D, PIT-C, MoCA-K, KQOL-AD, and cost analysis variables, we will use linear mixed models that include baseline score (if there is a measured value before the intervention) as covariates and the trial centers as fixed effect variables. For efficacy assessment of RCFT, DST, K-BNT, calculation, COWAT, K-CWST, DSC, K-TMT-E variables, we will use the covariance analysis model that includes baseline score (if there is a measured value before the intervention) as covariates and the trial centers as fixed effect variables. For efficacy assessment of CTIS, BPPA, BIA, WED, and fNIRS continuous variables, we will use linear mixed models. In the case of categorical variables, we will present a contingency table and evaluate them in an exploratory way.

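### LOCF is the only stated missing-data rule, but SVLT-E is not tested between baseline and week 12, so anyone leaving before week 12 is scored as exactly zero change on the primary endpoint

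*Protocol article*

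**What the plan says.** Section 2.8 (Statistical analysis) names an intention-to-treat population, analysed first by full analysis set and then per protocol. Its rule for missing data is "Missing values will be imputed by the last-observation-carried-forward method". No exception is made for the primary endpoint.

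Section 2.9.1 (Primary outcome) defines that endpoint on SVLT-E: "The primary endpoint will be the change in score from baseline to 12 weeks". It is analysed by ANCOVA with an SVLT-E covariate and centre.

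Section 2.4 (Study procedure) gives the test schedule. At visit 1, after randomization, "subjects will undergo assessments for primary and secondary endpoints (SVLT-E, RCFT, DST, Calculation" and the remaining tests are done. Visits then follow at two-week intervals: "They will visit the trial center for evaluation of any changes or adverse effects every 2 weeks". The later tests are listed as "Visit 4 (WED, fNIRS, MoCA-K, PIT-C, EQ-5D, KQOL-AD); Visit 7 (all tests); and Visit 8 (SVLT-E, Cost analysis" and a few further scales.

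Section 2.7 (Sample size calculation) assumes "a 20% dropout rate". Section 2.9.2 (Secondary outcomes) adds only week 24 as a further SVLT-E time point. For the repeated outcomes it says: "For efficacy assessment of SVLT-E, MMSE-DS, EQ-5D, PIT-C, MoCA-K, KQOL-AD, and cost analysis variables, we will use linear mixed models that include baseline score".

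**The concern.** LOCF needs an intermediate measurement to carry. The primary endpoint has none, so the rule becomes baseline carried forward and every imputed change is exactly 0. On a memory test, zero is not a neutral value: retest gain would push the mean change up and disease progression would push it down. The imputed zeros also enter the ANCOVA as if they had been measured, with no allowance for uncertainty.

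Two further consequences follow from the same sentence. For the week-24 SVLT-E endpoint, an end-of-treatment value is carried across 12 untreated weeks. For the repeated secondary outcomes, a literal reading fills the gaps before linear mixed models are fitted, although those models can use incomplete records without imputation.

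At stake are the size of the single primary estimate and, if the arms lose participants at different rates, its direction and error rate.

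**Working it through.** **1. Which SVLT-E values exist.** With two-week visits, visit 4 is week 6 and visit 7 is week 12. Between visits 1 and 7 the text lists "Visit 2 (Blind test); Visit 4 (WED, fNIRS, MoCA-K, PIT-C, EQ-5D, KQOL-AD); Visit 7 (all tests". SVLT-E is absent from visits 2 and 4, and no efficacy test is listed at visits 3, 5 or 6. Visit 8 (week 24) comes too late to be carried to week 12. A participant who leaves before visit 7 has only the baseline SVLT-E.

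**2. The protocol's own sample size.** Inputs from section 2.7: 80% power, significance level 0.05 (taken as two-sided), effect 0.7 (printed with a percent sign, read as 0.7 SD), 20% dropout.
- n per arm = 2 × ((1.960 + 0.842)/0.7)² = 32.04
- 32.04/(1 − 0.20) = 40.04 per arm, or about 80 in total

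The stated 80 reproduces. At 20% dropout, 0.20 × 80 = 16 participants (8 per arm) could be given a change of 0.

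**3. Expected LOCF difference.** Let m be the mean change on placebo, e the treatment effect, and pT and pC the dropout shares on JDH and placebo, with dropout unrelated to outcome. Then

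E[difference] = (1 − pT)(m + e) − (1 − pC)m = (1 − pT)e + (pC − pT)m.

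The first term is attenuation. The second is a spurious difference that needs both unequal dropout and a non-zero mean change.

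| Case | Arithmetic | Result (SD) |
|---|---|---|
| e = 0.7, 20% in both arms | 0.8 × 0.7 | 0.56 |
| e = 0, equal dropout | 0 | 0 |
| e = 0, unequal dropout, m = 0 | 0 | 0 |
| e = 0, JDH 10%, placebo 30%, m = +0.5 | 0.2 × 0.5 | +0.10 |
| e = 0, JDH 30%, placebo 10%, m = +0.5 | −0.2 × 0.5 | −0.10 |
| e = 0, JDH 30%, placebo 10%, m = −0.5 | −0.2 × −0.5 | +0.10 |
| e = 0, JDH 15%, placebo 25%, m = +0.5 | 0.1 × 0.5 | +0.05 |
| e = 0.7, JDH 30%, placebo 10%, m = +0.5 | 0.49 − 0.10 | 0.39 |

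Only the effect of 0.7 and the overall 20% dropout come from the protocol. The split by arm and m are assumptions.

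**4. Power and type I error.** These come from simulation: 40 per arm, ANCOVA on change adjusted for baseline (centre omitted), SD of change 1, baseline/follow-up correlation 0.6 (assumed), dropout unrelated to outcome.
- Equal 20% dropout, e = 0.7: power with LOCF is about 80% at m = +0.5 and about 84% at m = 0 (slightly higher still at m = −0.5). With observed cases it is 86%.
- Equal dropout, e = 0: type I error near 5%.
- 10% v 30%, m = ±0.5, e = 0: type I error about 8 to 9%, or just under 8% if the number of dropouts per arm is held fixed.
- 15% v 25%, m = +0.5, e = 0: about 6% (5% with fixed numbers).
- 10% v 30%, m = 0, e = 0: near 5%.
- JDH 30%, placebo 10%, m = +0.5, e = 0.7: power about 46%.

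**The case against.** Whether 0.56 is biased depends on the estimand. If participants who stop JDH then follow the placebo course, the intention-to-treat difference at equal 20% dropout is itself 0.8 × 0.7 = 0.56. LOCF then gives the right mean difference, and imputation under missing-at-random would aim at 0.70. This stands: the attenuation is bias only if dropouts would have kept the effect.

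Under the protocol's own inputs the harm is modest. Power stays at or above the planned 80% or very close to it, and there is no false-positive inflation. The larger distortions need a threefold dropout imbalance and a half-SD mean change, neither of which is in the article. This also stands.

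The full analysis set is not defined and Table 1 is not shown, so dropouts might be excluded rather than imputed, or an early-termination SVLT-E might exist. Neither is stated: section 2.8 says intention to treat without such an exclusion, and section 2.4 lists the tests by visit. The count of 16 is therefore an upper figure for those leaving before week 12. The per-protocol analysis, probably close to a completers' analysis, is a partial check.

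That LOCF precedes the mixed models is an inference from one general sentence. Section 2.9.2 does not say that imputed data enter those models.

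**Conclusion.** The point holds, and should be fixed. As written, LOCF on the primary endpoint is baseline carried forward for anyone who leaves before week 12. At the protocol's own effect and dropout, the expected estimate falls from 0.70 to 0.56 SD if dropouts would have kept the benefit, with a loss of roughly 2 to 6 percentage points of power (86% to between 84% and 80%). With assumed unequal dropout and non-zero mean change, the bias can run either way, so LOCF is not reliably conservative. With a decline and more dropout on JDH, it favours JDH.

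A reader might infer that the primary estimate is biased whatever happens, or that false positives are inflated under the plan's own assumptions. The documents do not support either. There is no bias when dropout is equal and there is no effect, nor when there is no effect and no mean change. Type I error rises only in scenarios that the article does not state.

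**What to change.** Replace the LOCF sentence in section 2.8.
- **Primary:** the stated ANCOVA of week-12 SVLT-E change (treatment, baseline SVLT-E, centre) after multiple imputation under missing-at-random, by arm, using baseline, centre and the week-6 MoCA-K already collected at visit 4.
- **Repeated secondary outcomes, including SVLT-E at week 24:** the linear mixed models of section 2.9.2, with no prior LOCF.
- **Sensitivity:** LOCF, labelled as such, beside a reference-based or delta analysis that covers the case where dropouts lose the treatment benefit.

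A mixed model of SVLT-E at weeks 12 and 24 is a possible alternative for the primary, but it is not equivalent. Participants who leave early normally have neither value and add almost nothing to it, and it does not use the week-6 MoCA-K.

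The cost is a wording change before unblinding and a little more analysis work. No new patients, visits or data are needed.

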### Efficacy assessment

2.9

#### Primary outcome

2.9.1

The primary outcome will be measured by SVLT-E. The primary endpoint will be the change in score from baseline to 12 weeks. For efficacy assessment, we will use the covariance analysis model that includes the SVLT-E scores as covariates and the trial centers as fixed effect variables.

#### Secondary outcomes

2.9.2

The secondary outcomes will be measured by SVLT-E, RCFT, DST, calculation, K-CWST, DSC, K-TMT-E, COWAT, K-BNT, MMSE-DS, MoCA-K, PIT-C, EQ-5D, KQOL-AD, cost analysis, CTIS, BPPA, BIA, WED, and fNIRS. The secondary endpoints will include change in SVLT-E score from baseline to 24 weeks; change in RCFT, DST, K-BNT, calculation, COWAT, K-CWST, DSC, K-TMT-E, MMSE-DS scores from baseline to 12 weeks; change in EQ-5D, PIT-C, MoCA-K score from baseline to 6, 12, and 24 weeks; and change in KQOL-AD score from baseline to 6, 12, and 24 weeks. The cost analysis (performed at 0, 12, and 24 weeks), CTIS, BPPA, and BIA values (0, 12 weeks), and WED and fNIRS values (0, 6, 12 weeks) will also be secondary endpoints. For efficacy assessment of SVLT-E, MMSE-DS, EQ-5D, PIT-C, MoCA-K, KQOL-AD, and cost analysis variables, we will use linear mixed models that include baseline score (if there is a measured value before the intervention) as covariates and the trial centers as fixed effect variables. For efficacy assessment of RCFT, DST, K-BNT, calculation, COWAT, K-CWST, DSC, K-TMT-E variables, we will use the covariance analysis model that includes baseline score (if there is a measured value before the intervention) as covariates and the trial centers as fixed effect variables. For efficacy assessment of CTIS, BPPA, BIA, WED, and fNIRS continuous variables, we will use linear mixed models. In the case of categorical variables, we will present a contingency table and evaluate them in an exploratory way.

### Safety assessment and adverse events report

2.10

Change in laboratory test results will be clinically evaluated. Interviews about adverse events and vital signs will be performed at every visit will be reported for safety assessment.

#### Safety assessment

2.10.1

Safety assessment will be performed comprehensively for the FAS and PP groups. A list of adverse events including occurrence time, frequency, severity (mild, moderate, severe), and intervention causality (definitely related, probably related, possibly related, probably not related, definitely not related, unknown) will be presented, with graphs if necessary. If statistical analysis is required, the paired *t*-test, McNemar test, analysis of variance, *t*-test, Chi-square test, and/or Fisher exact test will be performed according to the characteristics of the variables and purpose of the statistical evaluation.

#### Adverse events report

2.10.2

The investigator in charge will be required to report any adverse events during the trial to the PI within 24 hours, regardless of whether or not they are related to the intervention. In the case of a severe adverse event, the PI should stop the trial until further instruction is given, notify the client immediately, and provide an additional detailed report within 5 days. The client should promptly report to the other relevant investigators, the Institutional Review Board (IRB), and the Director of the Ministry of Food and Drug Safety.

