### Monitoring

2.12

An independent monitoring staff will be responsible for supervising the trial process, and will periodically review and verify whether the trial is being conducted and documented in accordance with the plan, standard work guidelines, and relevant regulations. Monitoring will be performed by calling and visiting the investigator. When visiting, the monitoring staff will check the documents and from this trial, and consult the investigator if there is any problem.

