### Ethics and dissemination

2.13

This trial will be performed in accordance with the Declaration of Helsinki, ICH-GCP (International Council of Harmonization-Good Clinical Practice) guidelines, Pharmaceutical Affairs Law, and all other applicable regulations. It has been approved by the IRB of the Daejeon University Dunsan Medical Center (DJDSKH-18-DR-16) since August 31, 2018. Any protocol deviations will be approved by the IRB of the Daejeon University Dunsan Medical Center. All participants or authorized surrogates will be given a detailed explanation about this trial with the consent form and given appropriate time to determine consent or assent.

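### Section 2.10.2 triggers expedited safety reporting by a *severe* adverse event, the word section 2.10.1 uses for the top intensity grade, where *serious* appears to be meant

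*Protocol article*

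**What the plan says.** Section 2.10.2 (Adverse events report) sets out three layers of reporting.

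- **Every adverse event.** The investigator is "required to report any adverse events during the trial to the PI within 24 hours", whatever the cause.
- **The escalated case, PI's duties.** "In the case of a severe adverse event, the PI should stop the trial until further instruction is given". The sentence goes on to have the PI "notify the client immediately, and provide an additional detailed report within 5 days".
- **The escalated case, client's duties.** "The client should promptly report to the other relevant investigators, the Institutional Review Board (IRB), and the Director of the Ministry of Food and Drug" (the quotation stops within the Ministry's name). This sentence has no trigger word of its own. It follows directly on the previous one and is naturally read as its continuation.

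Section 2.10.1 (Safety assessment) says what the adverse event listing will contain, including "severity (mild, moderate, severe), and intervention causality".

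Section 2.13 (Ethics and dissemination) states: "This trial will be performed in accordance with the Declaration of Helsinki, ICH-GCP". It adds the Pharmaceutical Affairs Law and other applicable regulations.

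**The concern.** Intensity and seriousness are separate properties of an adverse event. Intensity grades how strong the event is. Seriousness, in ordinary trial usage, concerns its outcome or consequence, such as death or admission to hospital. A moderate reaction that leads to admission is serious but not severe. A severe headache that resolves is severe but not serious.

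Expedited reporting to a sponsor, an ethics board and a regulator is normally driven by seriousness. Section 2.10.2 instead uses the word that the section just before it uses for an intensity grade. If a site applied that word as written, a serious event graded mild or moderate would have no stated route beyond the PI. The client, the other centres, the IRB and the Ministry would have no stated prompt notice of it.

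**Working it through.** There is no figure to reproduce and no formula applies. The check is a comparison of the sections.

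1. **What *severe* means in the article.** As a description of adverse events the word occurs in two places: the three-level scale in 2.10.1 and the trigger in 2.10.2. Only 2.10.1 gives it a meaning, as the top of mild, moderate, severe. Section 2.10.2 does not refer back to that scale, but it offers no other meaning.

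2. **Whether seriousness enters by another route.** The word *serious* does not appear in the article, and 2.10.2 attaches no outcome-based criterion to the trigger.

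3. **What the attached actions suggest.** Immediate notice to the client, a detailed report within 5 days, and a prompt report to the other investigators, the IRB and the Ministry together look like a serious-event procedure. Section 2.13 also commits the trial to ICH-GCP. Both indicate that *serious* was intended.

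4. **What the literal rule does with two kinds of event.**

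| Event | Report to PI within 24 hours | Immediate notice, 5-day report, onward report | Trial stop |
|---|---|---|---|
| Serious, graded mild or moderate | Yes | Not stated | Not stated |
| Severe, not serious | Yes | Yes | Yes |

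   The first row is the safety gap. The second is the reverse error: an intense but medically minor event would set off the whole procedure.

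5. **What happens if the word is swapped throughout.** The reporting gap closes. But the stop sits in the same sentence and carries no causality condition. It would then apply to every serious event, including a hospital admission unrelated to the tablets, in a three-centre trial of 80 people aged 45 to under 85. The reporting duties and the stop should therefore be considered separately.

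The article gives no adverse event rate, so the number of events affected cannot be estimated.

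**The case against.** The strongest reply is that this is a translation slip whose intent is plain, in a journal article that condenses protocol version 2.1 of 28 August 2018. The sites work from that protocol, which may use the right word. All adverse events reach the PI within 24 hours, so a serious but non-severe event is not lost at site level. ICH-GCP and Korean law apply in any case.

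Much of this stands, and it keeps the severity low. It does not remove the point. The allowance for condensed articles covers detail left out, and here the trigger is stated, with the wrong word. The 24-hour rule stops at the PI. A general commitment to ICH-GCP does not say which reading of 2.10.2 site staff should apply.

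A reader might infer more than the documents support:

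- **That the printed word governs conduct because the monitor checks against it.** Section 2.12 has the monitor "periodically review and verify whether the trial is being conducted and documented in accordance with the plan", alongside work guidelines and regulations. The article is not shown to be that plan.
- **That the lack of a definition of a serious adverse event is itself a defect.** An article commonly leaves such a definition to the full protocol. Only the trigger word is at issue.
- **That serious events will in fact go unreported.** This would require a site to read one word literally, against the evident purpose of the paragraph and the commitments in 2.13.

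**Conclusion.** Wrong as written, with low severity. Section 2.10.2 states the trigger for expedited reporting with a word that the article otherwise uses only for an intensity grade. Taken literally, serious events graded mild or moderate have no stated expedited report beyond the PI.

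The conclusion rests on two readings. The first is that *severe* in 2.10.2 carries the meaning it has in 2.10.1, the only one the article gives. The second is that the client's onward report depends on the same trigger, which is natural but not explicit. That *serious* was intended is an inference from the actions and from 2.13; the wording of version 2.1 itself cannot be seen.

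The harm is limited by the 24-hour report to the PI and by the regulatory commitments. The sample size, the significance level and the efficacy analysis are unaffected.

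**What to change.** In 2.10.2, make the immediate notice to the client, the 5-day detailed report and the client's onward report follow *a serious adverse event (as defined in ICH-GCP, whatever its severity grade)*. Attach that trigger explicitly to the onward report as well. Leave the grades in 2.10.1 and the 24-hour rule as they are. If version 2.1 has the same word, correct it there too.

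Decide the trial stop separately and state the choice:

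- **If the stop follows the corrected word**, any serious event halts the trial, including an unrelated hospitalisation, because there is no causality condition.
- **If the stop stays on *severe***, an intense but non-serious event can halt the trial, and a serious event of lower grade does not.

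The reporting correction costs one phrase and a division of the sentence, with no added visit or procedure. It means expedited reports for serious events graded mild or moderate. Severe but non-serious events would lose the expedited report, but would still reach the PI within 24 hours and still be listed by grade.
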